### Sample size and power calculation

The primary outcome is a change in HADS score at 3 months. A clinically relevant difference between groups would be a reduction in the total sum score of 2. In a previous study [36], the change within each group was normally distributed with a standard deviation (SD) of 2.5. We have here used a more conservative estimate with an SD of 4. Under these assumptions with a risk of type 1 error of 0.05 and a power of 0.8, 64 patients should be included in each group. Due to the risk of dropout of patients included in this type of trial, the total number of patients included is increased by 15% to 148 patients

STATA II, the Ralloc programme is used for randomization, permuting random block sizes of 2,4 and 6.

To assess the spontaneous variation in HADS scores over time, we will investigate a non-randomized group of 40 matched patients (relative to inclusion and exclusion criteria) without signs of psychological distress (i.e. HADS A < 8 and HADS D < 8) at first measurement with re-evaluation after 3 and 6 months. With 64 patients in the usual care arm and assuming a SD of 4 as above, we will have 80% power to detect a difference in change in HADS score (delta HADS) of 2.3 or more between these two groups.

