### Participants

The trial is a multi-centre trial planned to include 188 patients from three departments of cardiology. The main trial includes 148 randomized patients. We will also include a non-randomized subgroup of 40 matched patients (relative to inclusion and exclusion criteria) without signs of psychological distress to investigate spontaneous variation in HADS scores over time.

Inclusion criteria are:
Referred to CR and accepting CRPatients with newly diagnosed CAD and/ or surgically treated VHDHADS score > 8 for HADS-A and/or HADS-DAge < 65 yearsAble to speak and understand Danish

Exclusion criteria are:
EF < 35%Other serious comorbidity expected to have a serious impact on life expectancyKnown abuse of alcohol or euphoric drugsKnown more serious psychopathology such as schizophrenia, bipolar disorder, severe personality disorder and treatment with psychoactive drugs

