### Statistical analysis

The primary analysis will be a comparison of the intervention and control group in mixed-models linear regression with robust standard errors with 3-month values as outcome, and baseline and 6 months values will be used as adjustment variables. Analyses will also be adjusted for the centre and tested for treatment-centre interaction. For the analysis of the secondary outcomes return to work (yes/no), HbA1c< 48, BP< 135/85 mmHg, BMI< 30, LDL< 1.4 mmol/l and physical activity, we will also apply repeated measures regression. For adherence to CR (> 80%), we will compare groups by logistic regression adjusting for the centre. For the outcome of re-admission at 12 months, we will compare outcomes across groups with Kaplan-Meier curves and time-to-event analyses (Cox regression) adjusting for age, left ventricular ejection fraction, co-morbidities and risk factors as described above. A two-sided P < 0.05 will be considered statistically significant, and all primary outcome analyses will be performed without knowledge of group allocation.

We will compare the primary outcome in intervention and control groups with the spontaneous variation in the non-distressed subgroup of 40 participants by separate mixed-models linear regression adjusting for baseline values and centre.

The primary reported analyses will be carried out as a modified intention-to-treat as participants with missing data on a primary or secondary outcome will be excluded from the corresponding analyses. The analysis is supplemented with per-protocol analyses defined by participation in ≥ 4 of the 5 group-based sessions. Missing information on other co-variates will be permuted if there is < 20% missing data for the co-variate in question.

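### The 80% power for a 2.3-point difference sets 64 usual-care patients counted after dropout against 40 non-distressed patients counted before any; like for like it is about 77%, or 2.4 points

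*Protocol article*

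**What the plan says.** All the figures are in the protocol article.

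- **Primary comparison (Sample size and power calculation).** The target is a 2-point difference in HADS change at 3 months, and on the SD the text says "We have here used a more conservative estimate with an SD of 4". The result is "with a risk of type 1 error of 0.05 and a power of 0.8, 64 patients should be included in each group". Dropout is the reason given for enlarging the trial: "the total number of patients included is increased by 15% to 148 patients". With 1:1 randomisation that is 74 per arm.
- **Comparison with the non-distressed group (same section).** The claim opens "With 64 patients in the usual care arm and assuming a SD of 4 as above, we will have 80% power to detect"; the figure it then gives is 2.3 points of HADS change, set against the 40 non-distressed patients.
- **Size of that group (Participants).** The "non-randomized subgroup of 40 matched patients" is added to the 148 to make a planned total of 188, so 40 is the number enrolled.
- **Missing outcomes (Statistical analysis).** "participants with missing data on a primary or secondary outcome will be excluded from the corresponding analyses". The same section plans a formal mixed-model comparison of the randomised arms with these 40.

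**The concern.** The two sides of the second power statement are counted at different stages. Usual care enters at 64, when 74 are to be enrolled. The non-distressed group enters at 40, when 40 are to be enrolled. The statement therefore allows for loss on one side and assumes complete follow-up on the other.

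Loss among the 40 is plausible on the article's own terms. They are to be re-evaluated at 3 and 6 months and are matched on the entry criteria, which include an age limit below 65. The section on trial procedure treats working schedules as a threat to follow-up. Because participants with a missing outcome leave the analysis, each patient lost comes directly off the 40.

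At stake is the stated sensitivity of a secondary, non-randomised comparison. A reader weighing a null or borderline result would rely on a detectable difference that is somewhat too favourable.

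**Working it through.** **Inputs.** Difference 2 (primary) and 2.3 (second comparison), SD 4, power 0.80, 64 per arm, 148 randomised and 40 non-distressed are from the sample size section. The two-sided 0.05 level is from Statistical analysis. The 1:1 allocation is from the Abstract.

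**Method.** Two-sample t-test. The standard error is SE = 4 × √(1/n₁ + 1/n₂), the noncentrality is difference/SE, and power comes from the noncentral t distribution. The detectable difference is the one that gives 80% power.

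**Step 1: reproduce the plan's figures.**
- Primary: difference 2, SD 4 gives 63.8, rounded up to 64 per arm. Power at 64 per arm is 80.1%.
- Enlargement: 128 × 1.15 = 147.2, rounded up to 148, or 74 per arm.
- Second comparison, 64 versus 40: SE = 4 × √(1/64 + 1/40) = 0.806; 2.3/0.806 = 2.85; power 80.7%; detectable difference 2.28.

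All of the plan's figures reproduce. The 2.3 is correct for 64 and 40 analysed patients.

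**Step 2: the loss built into the 64.** 1 − 64/74 = 13.5%. This follows from the plan's own numbers and does not require reading the 15% as a dropout rate.

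**Step 3: the same loss in the 40.** 40 × 64/74 = 34.6. SE = 4 × √(1/64 + 1/34.6) = 0.844; 2.3/0.844 = 2.72.

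| Analysed (usual care v non-distressed) | Basis | Power for 2.3 | Detectable at 80% |
|---|---|---|---|
| 64 v 40 | plan: loss on one side only | 80.7% | 2.28 |
| 64 v 39 | one of the 40 lost | 80.1% | 2.30 |
| 64 v 38 | two of the 40 lost | 79.4% | 2.32 |
| 64 v 34.6 | 13.5% loss on both sides | 77.0% | 2.39 |
| 63 v 34 | assumed 15% loss on both sides | 76.3% | 2.41 |
| 74 v 40 | no loss on either side | 82.8% | 2.22 |

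The last row is also like for like, but the plan does not use it, because it takes 64 for usual care. Losing two of the 40 already takes power just below 80%.

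**Step 4: the primary comparison, for completeness.** 148 × 0.85 = 125.8, or 62.9 per arm, which gives 79.5% power by the t-test (80.1% by the normal approximation). Keeping 128 after a 15% loss would take 128/0.85 = 150.6, so 151. The 148 keeps 128 at a loss of up to 1 − 128/148 = 13.5%.

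**The case against.** The strongest reply is that no stated figure is wrong. The power sentence is conditional on 64 and 40 and reproduces for those numbers. No loss rate is given for the non-distressed group, so any figure applied to it is an assumption. The group is not randomised and serves to describe spontaneous variation and to judge when to screen; moving from 2.3 to 2.4 points would change no decision about treatment. The article also describes flexible scheduling, reminders and telephone contact to limit loss.

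Much of this stands, and it keeps the point small. It does not remove the mismatch. The sentence chooses the post-dropout number on one side and the enrolled number on the other, and 13.5% is the plan's own implied allowance. Measures to limit loss apply as much to usual care, where the plan still allows for it.

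A reader might go further and infer that the enlargement to 148 is an arithmetic error that costs the trial its primary power, since adding 15% is not the same as dividing by 0.85. The document does not support that. It says only that the total was increased by 15%, which is true, and it never states an expected dropout of 15%. Even if 15% were lost, primary power would be 79.5%, and the shortfall against 151 is three patients (four with equal arms, 2 × 76 = 152).

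**Conclusion.** The point holds for the comparison of usual care with the non-distressed group, and only there. With the same loss on both sides, the stated 80% power for 2.3 points becomes about 77%, and the difference detectable with 80% power is about 2.4 points. At an assumed 15% loss on both sides the figures are 76% and 2.41. This rests on SD 4 in both groups, a two-sided 0.05 level, a simple two-sample comparison as in the plan's own calculation, and loss among the non-distressed similar to that allowed in usual care. The documents give no separate rate for that group.

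It is a minor correction to a secondary, non-randomised comparison. The sample size of the randomised trial stands: primary power is about 80% with or without the refinement.

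**What to change.** In the sample size section, restate the second power figure with both groups counted after the same loss: with about 64 usual-care and 34 to 35 non-distressed patients analysed, the detectable difference at 80% power is about 2.4 points, or power is about 76–77% for 2.3. If 40 is meant as the number analysed, say so and state that 2.3 assumes no loss in that group.

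As a clarification only, add that 148 keeps 64 per arm at up to 13.5% loss, so that the 15% increase is not read as the tolerated dropout rate.

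Neither change alters enrolment, the analysis or the primary power. The cost is a sentence or two of rewording and one slightly less favourable figure.

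### The 80% power for a 2.3-point difference against the 40 non-distressed patients belongs to an unadjusted comparison of change, not to the baseline-adjusted model that is planned

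*Protocol article*

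**What the plan says.** All references are to the protocol article.

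- **Sample size and power calculation** sizes the randomised comparison first: "with a risk of type 1 error of 0.05 and a power of 0.8, 64 patients should be included in each group". On the SD it says "We have here used a more conservative estimate with an SD of 4".
- The same section then turns to the 40 extra patients, who are "without signs of psychological distress (i.e. HADS A < 8 and HADS D < 8) at first measurement". The claim for them reads "With 64 patients in the usual care arm and assuming a SD of 4 as above", followed by "we will have 80% power to detect a difference in change in HADS score (delta HADS) of 2.3 or more between these two groups".
- **Design** defines the randomised patients by a HADS-A or HADS-D of at least 8. The inclusion list under **Participants** requires a score above 8.
- **Statistical analysis** compares each randomised arm with the 40 patients "by separate mixed-models linear regression adjusting for baseline values and centre". On the test level it says "A two-sided P < 0.05 will be considered statistically significant".

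The article states no baseline HADS mean or SD and no correlation or slope between baseline and follow-up.

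**The concern.** The power sentence and the analysis sentence describe different calculations for one contrast. The power sentence is about a plain difference in change. The analysis compares the groups at equal baseline HADS, which is another estimand with another standard error.

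In a randomised comparison, baseline adjustment normally helps precision. Here it costs precision, because baseline HADS decides which group a patient is in. A non-distressed patient has a total of at most 7 + 7 = 14. A distressed patient has a total of at least 8 (at least 9 under the inclusion list). The groups share only a narrow band of totals, and the adjusted group effect rests on that band and on the assumed straight line through both groups.

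At stake is how the result can be read. If the adjusted contrast is not significant, the article's 80% would suggest that a difference of 2.3 points had been fairly tested, when the planned model may have much less power than that.

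**Working it through.** **1. Reproduce the stated figure.** Inputs from the article: n = 64 and 40, SD of change 4, two-sided 0.05, power 80%.

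- SE = 4 × √(1/64 + 1/40) = 4 × 0.2016 = 0.806.
- Detectable difference = (1.960 + 0.842) × 0.806 = 2.26, or 2.28 with the t distribution. This rounds to 2.3.
- Power at 2.3 = Φ(2.3/0.806 − 1.960) = Φ(0.893) = 81.4%, or 80.7% with the noncentral t.

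The figure is correct for an unadjusted comparison.

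**2. Add the planned adjustment.** With baseline HADS in the model, SE = s × √[(1/64 + 1/40) × VIF], where s is the residual SD and VIF = 1/(1 − R²) from regressing group on baseline HADS. Equivalently, VIF = 1 + p(1 − p) × gap²/W, where p = 64/104, gap is the difference in mean baseline total and W is the pooled within-group variance of baseline.

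Assumptions not in the article, central case: HADS-A mean 6, SD 4; HADS-D mean 4.5, SD 3.5; correlation 0.6; scores rounded and limited to 0–21.

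- Rule of at least 8: mean totals 16.58 and 6.75, gap 9.83; SDs 4.16 and 3.78, so W = (64 × 17.31 + 40 × 14.29)/104 = 16.1. VIF = 1 + 0.2367 × 96.6/16.1 = 2.42.
- Rule of above 8: gap 11.04, W = 15.15, VIF = 1 + 0.2367 × 121.9/15.15 = 2.90.

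**3. Residual SD.** If the article's 4 is the SD of change and b is the slope of follow-up on baseline, then s² = 16 − (1 − b)² × W. For b = 0.5 and the rule of at least 8, s² = 16 − 0.25 × 16.1 = 12.0, so s = 3.46 and SE = 3.46 × 0.2016 × √2.42 = 1.08. Power at 2.3 = Φ(2.3/1.08 − 1.96), about 56%. The detectable difference is 2.80 × 1.08 = 3.0.

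| Slope b | Power at 2.3, rule ≥ 8 | Detectable difference | Power at 2.3, rule > 8 | Detectable difference |
|---|---|---|---|---|
| 0.3 | 73% | 2.5 | 63% | 2.8 |
| 0.5 | 56% | 3.0 | 48% | 3.4 |
| 0.7 | 49% | 3.3 | 42% | 3.7 |
| 0.8 | 47% | 3.4 | 40% | 3.8 |
| 0.9 | 45% | 3.5 | 39% | 3.8 |

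Simulated ANCOVA (4,000 runs) came within about 2 percentage points of these values at the slopes simulated (0.3, 0.5, 0.7 and 0.9).

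**4. Range.** Varying HADS-A mean 5.5–7, HADS-D mean 4–5, the SDs and the subscale correlation gives about 40–60% for slopes 0.5 to 0.9 (extremes 37% and 61%). At slope 0.3 the range is about 55–82%. The top comes from the widest distribution (HADS-A mean 7, HADS-D mean 5, both SD 4), where s = 2.58, VIF = 2.33 and SE = 0.79. Taking 4 as the residual SD itself, with VIF 2.42, gives 45% and a detectable difference of 3.5. Taking the earlier study's 2.5 as residual SD gives about 84%.

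**5. Would dropping the adjustment rescue the figure?** With no true group effect, the expected difference in change is (1 − b) × gap. In the central case (rule ≥ 8, then > 8) this is 1.0 or 1.1 points at slope 0.9, 2.0 or 2.2 at 0.8, and 4.9 or 5.5 at 0.5. Under the rule of at least 8, the unadjusted test would reject in about 22% of trials at slope 0.9, 68% at 0.8 and practically all at 0.5.

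**The case against.** Several points on the other side stand.

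- **The arithmetic is right.** The article says difference in change, and 2.3 points at 80% follows from its inputs. The defect is a mismatch between two sections, not a miscalculation.
- **No single corrected power can be read from the article.** A reader might infer that the true power is 45%. That value needs an assumed baseline distribution and takes 4 as the residual SD, the least favourable reading. A low slope, or a residual SD near the 2.5 that the article set aside, brings power close to or above 80%. A mixed model that uses the 6-month values as further outcomes could also recover some precision.
- **Regression to the mean is not a flaw in the planned analysis.** A reader might infer that the planned contrast is largely a selection artefact. The article plans the baseline adjustment, which is the usual guard against it. The artefact matters here only as the reason not to remove the adjustment, and its size turns on the slope.
- **The comparison need not be abandoned.** Leaving out the tests against the cohort is a matter of preference. Nor does the article say how a null result would be interpreted.
- **Dropout among the 40 is minor.** The 64 is the number before the 15% increase, and no allowance is stated for the 40. With 34 left, the unadjusted detectable difference moves only from 2.3 to 2.4.

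What does not stand is the reply that 2.3 points and 80% can remain as printed. The collinearity follows from the article's own group definitions, and the power sentence makes no allowance for it.

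**Conclusion.** The power sentence is wrong as written for the analysis that the article plans. Its 80% holds for an unadjusted comparison of change and does not carry over to a model adjusted for the variable that defines the groups.

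That conclusion rests on the text alone. The size rests on assumed HADS distributions, an assumed slope and a change SD of 4. On those assumptions the variance inflation is about 2.3 to 2.9, power at 2.3 points is about 40–60% for slopes 0.5 to 0.9 and about 55–82% at slope 0.3, and the detectable difference for slopes 0.5 to 0.9 is about 3.0 to 3.9 points.

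A reader might extend this to the trial's main result. The documents do not support that: the contrast is ancillary and non-randomised, and the randomised comparison with its 64 per group is untouched.

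**What to change.** Delete the sentence giving 80% power for 2.3 points, or restate it for the baseline-adjusted model with the assumed baseline distribution, slope and residual SD, and a range rather than one figure. Keep the baseline adjustment.

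As an option, make the cohort's own mean HADS change at 3 and 6 months, with a 95% confidence interval, its main result. The Design section wants the cohort in order to judge whether the first rehabilitation visit is the right time to screen, and this estimate addresses that directly. With n = 40 and SD 4 the half-width is 2.02 × 4/√40 = 1.3 points.

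The cost is a change of wording in the sample size section, and in the analysis section if the option is taken. No extra patients or data are needed. One published figure becomes less favourable.

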### Data management

Data will be collected at baseline and follow-up visits. Questionnaire responses (all on paper) will be entered into electronic form in REDCap immediately after the assessment. Data from patient records (all electronic) will also be entered into REDCap. All participants will be identified by unique study identification numbers that will be included in a password-protected file. Data will be stored in accordance with the rules of the Danish Data Protection Agency. REDCap meets all criteria for the handling of patient data in accordance with the laws on the processing of personal data. The principal investigator [name] will have unlimited access to the final trial dataset.

### Statistical analysis

The primary analysis will be a comparison of the intervention and control group in mixed-models linear regression with robust standard errors with 3-month values as outcome, and baseline and 6 months values will be used as adjustment variables. Analyses will also be adjusted for the centre and tested for treatment-centre interaction. For the analysis of the secondary outcomes return to work (yes/no), HbA1c< 48, BP< 135/85 mmHg, BMI< 30, LDL< 1.4 mmol/l and physical activity, we will also apply repeated measures regression. For adherence to CR (> 80%), we will compare groups by logistic regression adjusting for the centre. For the outcome of re-admission at 12 months, we will compare outcomes across groups with Kaplan-Meier curves and time-to-event analyses (Cox regression) adjusting for age, left ventricular ejection fraction, co-morbidities and risk factors as described above. A two-sided P < 0.05 will be considered statistically significant, and all primary outcome analyses will be performed without knowledge of group allocation.

We will compare the primary outcome in intervention and control groups with the spontaneous variation in the non-distressed subgroup of 40 participants by separate mixed-models linear regression adjusting for baseline values and centre.

The primary reported analyses will be carried out as a modified intention-to-treat as participants with missing data on a primary or secondary outcome will be excluded from the corresponding analyses. The analysis is supplemented with per-protocol analyses defined by participation in ≥ 4 of the 5 group-based sessions. Missing information on other co-variates will be permuted if there is < 20% missing data for the co-variate in question.

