**Fig. 1 Fig1:**
[figure not shown]
The trial diagram. Flow of patients. Participants in the intervention group follow CR and five sessions of CBT therapy and the control group follow standard CR

Randomization is performed by an independent researcher, and the randomization programme is kept in a secured, logged hard disk. STATA II, the Ralloc programme, permuting random block sizes of 2, 4 and 6, respectively, is used for randomization. Before randomization, baseline data are collected (see Table 1).

**Table 1 Tab1:** Schedule of enrolment, intervention and assessments

	Study period (months)								
	Baseline	Intervention (allocation) Group-based therapy (5 weeks)					Post-allocation (months)		Close-out
Timepoint	0	0	1 week	2 weeks	3 weeks	4 weeks	3 months	6 months	12 months

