### Primary outcome

The primary outcome is mean (method of aggregation) change (metric) in psychological distress (domain) measured by HADS total score (specific measurement) from baseline to three months (time) in the intervention group compared with the usual care group. This outcome may be subject to ascertainment bias when blinding is not possible, e.g. social desirability bias causing participants to respond more favourably. We have attempted to limit this by administering the paper questionnaires to be filled in unsupervised. Furthermore, since both the intervention and the control group receive usual CR in the same cardiac settings, both groups may be subject to similar social desirability bias. At the 6-month follow-up, we anticipate that this bias will be reduced.

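### The primary model adjusts the 3-month HADS comparison for the 6-month HADS score, which treatment can change, so it does not estimate the planned 3-month effect

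*Protocol article*

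**What the plan says.** The Primary outcome section of the protocol article defines the target as mean change in psychological distress, "measured by HADS total score (specific measurement) from baseline to three months (time) in the intervention group compared with the usual care group". The Statistical analysis section gives the primary model as a mixed-models linear regression with robust standard errors, with "3-month values as outcome, and baseline and 6 months values will be used as adjustment variables", plus adjustment for centre.

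Table 1 places the five CBT sessions at weeks 0 to 4 and HADS at baseline, 3 months and 6 months. Baseline data precede allocation ("Before randomization, baseline data are collected (see Table 1"), so baseline HADS is a legitimate covariate. The 6-month score comes after allocation, treatment and the primary time point. The Primary outcome section itself treats 6 months as an informative HADS assessment: "At the 6-month follow-up, we anticipate that this bias will be reduced".

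The comparison with the non-distressed subgroup, in the same Statistical analysis section, adjusts for baseline and centre only.

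**The concern.** A covariate in the primary comparison of a randomised trial should not be something the treatment can alter. If CBT lowers HADS at 3 months and part of that benefit remains at 6 months, the 6-month covariate absorbs part of the treatment effect. The arm coefficient then describes the 3-month difference among patients who have the same score three months later. That is not the baseline-to-3-month effect the trial was designed and sized to detect.

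Three consequences follow if the sentence is carried out as written:

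- With a sustained effect, the estimate shrinks towards zero and power falls.
- With a late effect, the model can show apparent harm at 3 months where there is none.
- A patient with a valid 3-month score but no 6-month score is either lost from the primary analysis or depends on an imputed later value.

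**Working it through.** **The plan's own figure.** The Sample size section takes a difference of 2 ("A clinically relevant difference between groups would be a reduction in the total sum score of 2") and an SD of 4 ("We have here used a more conservative estimate with an SD of 4"), with two-sided alpha 0.05 and power 0.80. The normal approximation gives n = 2 × (1.960 + 0.842)² × 4² / 2² = 62.8, so 63 per arm. The t-test gives 63.8, so 64, as stated. Then 128 × 1.15 = 147.2, so 148. The figure reproduces, and it assumes that the full 2 points are being estimated.

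**What the model estimates.** Let d3 and d6 be the treatment effects at 3 and 6 months (negative favours CBT). Let b6 be the within-arm slope of 3-month on 6-month HADS, given baseline. The arm coefficient in the model as written is

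d3 − b6 × d6,

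which equals d3 only if d6 = 0 or b6 = 0.

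**First set of assumptions.** Residual SD is 4 at both visits after baseline adjustment, there are 64 per arm, and the residual correlation between visits is ρ, so b6 = ρ. The standard error is 4 × √(1 − ρ²) × √(2/64), divided by √(1 − R²) because arm and 6-month score are correlated. Here R² = 0.25·d6² / (0.25·d6² + 16). For d6 = −2 this is 1/17, which multiplies the standard error by √(17/16) = 1.031.

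| d3 | d6 | ρ | Estimate | Power or rejection rate |
|---|---|---|---|---|
| −2 | −2 | 0.3 | −1.4 | about 52% |
| −2 | −2 | 0.5 | −1.0 | about 35% |
| −2 | −2 | 0.6 | −0.8 | about 27% |
| −2 | −2 | 0.7 | −0.6 | about 20% |
| −2 | −1 | 0.3 to 0.7 | −1.7 to −1.3 | about 67–72% |
| −2 | 0 | 0.6 | −2.0 | about 94% |
| 0 | −2 | 0.6 | +1.2 | about 53% |

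Worked example for ρ = 0.5: the standard error is 4 × 0.866 × 0.1768 × 1.031 = 0.631. Then 1.0 / 0.631 = 1.58, and power is Φ(1.58 − 1.96), about 35%. Simulation agrees: estimates near −1.0, −0.8 and −0.6, and power of 35–36%, 27% and 19–20%, for ρ = 0.5, 0.6 and 0.7. In the late-effect case it gave +1.21 with 53–54% rejection.

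**Second set of assumptions.** The SD of 4 is treated as the SD of the change score, as the Sample size section does. The SD at each visit is then 4 / √(2(1 − r03)), and b6 = (r36 − r03·r06) / (1 − r06²), where the r's are the correlations between the visits at 0, 3 and 6 months. With d3 = d6 = −2:

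| r03, r06, r36 | b6 | Estimate | Power as written | Power, baseline only |
|---|---|---|---|---|
| 0.3, 0.3, 0.3 | 0.231 | −1.54 | 0.76 | 0.94 |
| 0.5, 0.5, 0.5 | 0.333 | −1.33 | 0.60 | 0.90 |
| 0.7, 0.7, 0.7 | 0.412 | −1.18 | 0.48 | 0.87 |
| 0.5, 0.4, 0.7 | 0.595 | −0.81 | 0.37 | 0.90 |
| 0.6, 0.5, 0.8 | 0.667 | −0.67 | 0.31 | 0.89 |

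The loss is 23% to 67%. With a 1-point effect at 6 months it is 12% to 33%. With d3 = 0, d6 = −2 and correlations 0.5, 0.4, 0.7, the model rejected in 65% of simulated trials, in favour of control. The baseline-only model rejected in 5%.

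**The case against.** The strongest reply is that the sentence is badly worded and a repeated-measures model was meant. The paragraph speaks of mixed models, says repeated-measures regression will also be used for secondary outcomes, and adjusts the parallel subgroup comparison only for baseline and centre. That intention is plausible. But the sentence names the 3-month value as the outcome and puts the 6-month value with baseline as an adjustment variable, and no other part of the article corrects it. An analyst who follows it gets the wrong primary result, so the text needs changing on either reading.

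The second reply is that the size is uncertain, and this stands. The loss depends on correlations and a 6-month effect that the article does not state. It is modest if the effect half fades and nil if it disappears. The late-effect case is an illustration; nothing in the article predicts it. The lowest powers, 20% to 35%, come from using the SD of 4 as a baseline-adjusted residual SD. That also makes the benchmark for the correct model about 80% rather than 87–94%.

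Two side points should not be pressed. A mixed model with one outcome row per patient could still carry a random effect for centre or therapy group. The absence of 6-month HADS from the listed secondary outcomes may be settled in an analysis plan not shown here. Neither affects the main point.

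**Conclusion.** The concern holds: the primary analysis is wrong as written. The covariate is a post-treatment measurement of the outcome itself, so the arm coefficient does not estimate "from baseline to three months (time) in the intervention group compared with the usual care group" unless the 6-month effect is zero or the two visits are unrelated given baseline. The direction is certain for a sustained benefit with positively correlated scores: the estimate is pulled towards zero. Across the two sets of assumptions, a fully sustained 2-point effect is estimated at between −1.54 and −0.6, with power between about 76% and 20% at 64 per arm, compared with 80% or more when the 6-month score is left out. These figures rest on assumed between-visit correlations of 0.3 to 0.8. Because the fault lies in the primary estimate, its confidence interval and its P value, it must be corrected before the analysis.

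**What to change.** At a minimum, delete the 6-month value from the adjustment variables, so that the primary model is 3-month HADS on arm, baseline HADS and centre.

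If the 6-month data are to be used, which may have been the intention, model the 3- and 6-month scores jointly as repeated outcomes. Use fixed effects for arm, visit, arm-by-visit, baseline HADS (by visit) and centre, with an unstructured within-patient covariance. State that the arm contrast at 3 months is the primary result. The same model yields the 6-month contrast, which can be reported as a secondary outcome if it is added to that list.

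The cost is one sentence in the Statistical analysis section, and one entry under Secondary outcomes if the 6-month contrast is reported there. No new data are needed, because HADS is already collected at baseline, 3 and 6 months, and the sample size stands. The change should be dated and made before any comparison by arm; the article reports that enrolment was still open.
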